### Withdrawal

Subjects may voluntarily withdraw from the study at any time without having to provide a reason. If the subject’s compliance is poor, the principal investigator reserves the final right to remove it from this study.

Subjects may be withdrawn because of the following reasons:Major protocol deviationsDue to safety concerns, patients with AEs are not suitable for continued participation in this studyOther situations: based on the investigator’s discretion, the patient is no longer eligible for the study for any reasonMissed follow-up visit or death

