### Sample size

According to the results of the preliminary study, the cumulative incidence of severe gastric and duodenal bulb erosion and ulcers of the 1-month PPI treatment group is assumed to be 36%, and that of the 12-month PPI treatment group was assumed to be 18%. Based on a two-sided *α* of 0.05 and a randomization ratio of 1:1, a total of 186 subjects are required to provide a power of 80%. Considering a 20% drop-out rate, the sample size of 232 subjects was determined.

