### Definition of the end of study

The date on which the last subject completed the last follow-up was the endpoint of this studyDuring the follow-up period, if the patient’s biopsy pathological report showed that EGD detects precancerous lesions (e.g., atypical hyperplasia, low-grade or high-grade internal neoplasia, etc.) or malignant lesionsPatients randomized to the control group (1-month pantoprazole treatment group) should continue PPI treatment if GERD-Q questionnaire score ≥ 8, endoscopic findings of reflux esophagitis (LA-A and above), gastroduodenal mucosal injury of modified Lanza score of 4, or upper gastrointestinal bleeding at any time during the follow-up period

According to the ITT principle, all patients randomized in this study should be evaluated for primary and secondary endpoints regardless of changes in PPI treatment. Thus, patients in the 1-month pantoprazole treatment group required PPI treatment at any time after 1 month and could also be assessed for primary and secondary endpoints.

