### Trial status

Recruitment starts on October 20, 2019. A total of 236 patients were enrolled in the DACAB-GI-2 trial between October 2019 and February 2022. Among them, 183 patients who received an effective randomized intervention were included in the study. A 12-month clinical follow-up has been completed in 117 patients. Due to the outbreak of Omicron in March 2022, Shanghai is currently still in a city-wide lockdown. Some follow-up visits have had to be postponed for 2 to 3 months. The duration of the trial was extended with the approval of the ethics committee, and it is planned to be completed in June 2023. The version of this protocol is 4.0 (date 20220225).

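### The Withdrawal section permits removal from the study for poor compliance, a major deviation or a missed visit, against the plan's own rule to follow and evaluate everyone randomized

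*Protocol article*

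**What the plan says.** **Withdrawal.** Besides voluntary withdrawal, if a subject's "compliance is poor, the principal investigator reserves the final right to remove it from this study". Subjects may also be withdrawn for major protocol deviations, for adverse events, at the investigator's discretion for any reason, and for a missed follow-up visit or death.

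**Follow-up.** Patients are followed to 12 months after randomization, with death as the only exception named. Endoscopy is done at 6 and 12 months by an endoscopist blinded to allocation. The 12-month visit is at 360±14 days. The 3- and 9-month visits are telephone calls.

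**Definition of the end of study.** The list includes continued PPI treatment in control patients who meet certain reflux, Lanza score or bleeding criteria. The text after the list says that "all patients randomized in this study should be evaluated for primary and secondary endpoints regardless of changes in PPI treatment", and that control patients who needed a PPI after month 1 can still be assessed.

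**Statistical and analytical plans.** The primary analysis follows the ITT principle, and all randomized subjects are in the ITT set.

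**Data capture.** For subjects who withdraw early, the available efficacy and safety data are recorded. No collection after withdrawal is described.

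**Trial status.** "Some follow-up visits have had to be postponed for 2 to 3 months". The trial was extended with ethics approval.

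**The concern.** The plan does not distinguish stopping the study drug from leaving the study. The reasons that allow removal (compliance, deviation, a missed visit) all arise after randomization and can be related to treatment. The person deciding on removal knows the arm. Blinding the endoscopist protects the grading of an endoscopy but not whether it takes place.

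A patient removed before month 12 may never have the 12-month endoscopy, which belongs to the primary outcome. An analysis set defined as all randomized subjects does not supply an examination that was not done. If the removed patients differ in risk from those retained, and removal is more frequent in one arm, the comparison is no longer the randomized one.

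**Working it through.** **1. The rules side by side**

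| Event | Withdrawal section | Other sections |
|---|---|---|
| Poor compliance | Principal investigator may remove from the study | Follow-up: to 12 months unless dead. End of study: evaluated whatever happens to PPI treatment |
| Major deviation | May be withdrawn | ITT set: all randomized |
| Missed visit (which visit is not stated; could be a telephone call) | May be withdrawn | Follow-up: to 12 months unless dead |
| PPI continued in a control patient | Not named | Listed under end of study, yet still to be assessed |

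An investigator who uses the permission in the first three rows departs from the rules in the right-hand column. In the fourth row the text does settle that assessment continues, but the item sits under a heading that suggests the opposite.

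**2. Can the loss differ by arm?** The withdrawal wording is the same for both arms, but the exposure to it is not. After month 1 the 12-month arm has 11 more months of assigned pantoprazole, and the Intervention section bars that arm from H2 blockers and mucosal protective agents, which the control arm may take. Control patients can also breach the protocol, for instance by taking a PPI without one of the listed criteria. A difference between arms is therefore possible, with no certain direction.

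**3. The plan's planning figures.** From Sample size: 36% (1-month arm) against 18% (12-month arm), two-sided α 0.05, 80% power, 1:1.

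- Unpooled variance: (1.960 + 0.842)² × (0.36×0.64 + 0.18×0.82) / 0.18² = 7.849 × 0.378 / 0.0324 = 91.6, so 92 per arm, 184 in total.
- Pooled variance: 95 per arm, 190 in total.
- The stated 186 lies between these. 186 / 0.80 = 232.5, against the stated 232.

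The sample size reproduces and is not in dispute. Only its two event rates are used below.

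**4. Illustration, on assumed inputs.** Let w be the share of the 12-month arm removed, p_rem the risk in those removed and p_ret the risk in those retained.

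Rate in all randomized = (1 − w) × p_ret + w × p_rem. The excess over the observed rate is w × (p_rem − p_ret).

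The documents give neither w nor p_rem. Assume p_ret = 18%, p_rem = 36% (the control rate), and no removals from the control arm:

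| w | Rate in all randomized | True contrast with 36% | Observed contrast | Overstatement |
|---|---|---|---|---|
| 5% | 0.95×18 + 0.05×36 = 18.9% | 17.1 points | 18 points | 0.9 points |
| 10% | 0.90×18 + 0.10×36 = 19.8% | 16.2 points | 18 points | 1.8 points |
| 20% | 0.80×18 + 0.20×36 = 21.6% | 14.4 points | 18 points | 3.6 points |

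If p_rem = p_ret there is no bias. If the loss fell instead on higher-risk control patients, the contrast would be understated.

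**The case against.** The strongest defence is that the rules are permissive and arm-neutral, that compliance is not limited to pantoprazole, and that no withdrawals by arm are reported. A patient removed after month 6 may already have an endoscopy, Data capture keeps it, and the primary outcome is worded as within 12 months. Handling of missing data is commonly left to an analysis plan that is not shown. All of this stands, and it limits what can be said about size. It does not remove the contradiction: the protocol itself must say whether the examination is still sought, because no analysis plan can create it afterwards.

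Three stronger readings are tempting but not supported.

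- *Outcomes are lost from the 12-month arm only.* The text applies to both arms, and control patients can also deviate or miss visits. Only the possibility of unequal loss follows.
- *Patients delayed by the lockdown are removed.* A delay of 2 to 3 months exceeds the ±14-day window, but Trial status says that visits were postponed and the trial extended. It does not say that anyone was withdrawn or any late endoscopy discarded. COVID-related exclusion operates through the modified full analysis set, a separate mechanism. The gap between 236 enrolled and 183 counted as effectively treated (53 patients) comes from that count and does not measure removals for compliance.
- *Power falls substantially.* Computing power from the diluted rates in the illustration describes the effect of non-compliance when such patients are kept in the analysis, not the effect of removing them. Nor can the 183 − 117 = 66 patients without completed 12-month follow-up be counted as lost. Enrolment ran to February 2022, so many were probably not yet due.

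**Conclusion.** The point holds as a contradiction in the protocol. Withdrawal permits discretionary removal from an open-label study for reasons that arise after randomization, while Follow-up, Definition of the end of study and the ITT definition require everyone randomized to be followed and evaluated. Used as written, the permission can lose primary-outcome endoscopies, and the loss may differ by arm.

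The size and direction of any bias cannot be computed from the documents. The overstatement of 0.9 to 3.6 percentage points rests wholly on three assumptions: 5–20% of the 12-month arm removed, a 36% risk in those removed against 18% in those retained, and no removal from the control arm. It shows how the mechanism works and is not an estimate.

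**What to change.** Amend before analysis so that Withdrawal, Follow-up, Definition of the end of study and Statistical and analytical plans agree:

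1. Separate stopping study drug from leaving the study.
2. State that non-compliance, a protocol deviation, PPI use in a control patient, or a missed or late visit does not end outcome collection. Only withdrawal of consent, death or true loss to follow-up does.
3. Move the control-arm PPI item out of Definition of the end of study, so that it cannot be read as ending participation. This concerns outcome collection only and leaves the clinical content of the item as it is.
4. For visits postponed by the lockdown, state that a postponed visit is not a withdrawal and that the endoscopy is still collected. Pre-specify a sensitivity analysis by whether the endoscopy fell inside the visit window. No fixed wider window is proposed: a late endoscopy may be read after the planned treatment period, and whether that is acceptable for the main analysis is a trade-off for the trial team.

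The cost is amendment wording and continued follow-up of patients who are off study drug. The sample size does not change. Completion was planned for June 2023, after protocol version 4.0 of February 2022, which left time for the change.

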### Sample size

According to the results of the preliminary study, the cumulative incidence of severe gastric and duodenal bulb erosion and ulcers of the 1-month PPI treatment group is assumed to be 36%, and that of the 12-month PPI treatment group was assumed to be 18%. Based on a two-sided *α* of 0.05 and a randomization ratio of 1:1, a total of 186 subjects are required to provide a power of 80%. Considering a 20% drop-out rate, the sample size of 232 subjects was determined.

### Scope of study data

At the first visit, we will collect the demographic information of the participants, including age, gender, past medication history, medical history, smoking, and alcohol use history. The results of hemoglobin, platelet count, liver function, renal function, serum lipid analysis, HbA1c, and DIC tested for the first time after admission are used as baseline data. The above laboratory tests will be also collected and recorded at 6 and 12 months after randomization. ^13^C urea breath test should be done before enrollment.

### Outcome measurements

The primary outcome of this study will be the percentage of patients with gastroduodenal erosions and ulcers evaluated by EGD within 12 months after randomization. Gastroduodenal erosions and ulcers will be assessed according to the Lanza Endoscopic Scoring System [18] (0, normal; 1, mucosal hemorrhages only; 2, 1–2 erosions; 3, 3–10 erosions; 4, >10 erosions or an ulcer ≥3 mm). In addition, ≥1 ulcer with a diameter no less than 5mm will be grouped separately.

Secondary outcomes are as follows:Percentage of patients with gastroduodenal erosions and ulcers evaluated by EGD at 6 months after randomization.Cumulative rate of patients with upper gastrointestinal bleeding according to the modified TIMI criteria. According to the definition of non-CABG-related bleeding in the modified TIMI criteria, the severity of upper gastrointestinal bleeding is classified into 3 grades: major, minor, and minimal—(1) major: clinically overt signs of hemorrhage associated with a drop in hemoglobin of ≥5 g/dL; (2) minor: clinically overt signs of upper gastrointestinal bleeding, resulting in hemoglobin drop of 3 to <5 g/dL; and (3) minimal: any overt bleeding event that does not meet the criteria above.Percentage of patients with RE evaluated by EGD at 12 months after randomization. According to the Los Angeles classification, endoscopic reflux esophagitis was assigned a grade from A to D.Percentage of patients with RE evaluated by EGD at 6 months after randomization.

Other pre-specified outcomes (up to 12 months) include:The cumulative rate of patients with MACE (composite of cardiovascular death, myocardial infarctions, or stroke)The failure rate of grafts assessed by computed tomographic angiography or coronary angiography. Graft failure was assessed according to the modified Fitzgibbon classification [19]: stenosis ≥50% or occlusion of the graft or distal anastomosis (type B or O)The cumulative rate of patients with all-cause death

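### Upper GI bleeding grades are separated by measured hemoglobin drop alone, so a fatal or transfused bleed can be graded too mildly in the severity breakdown

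*Protocol article*

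**What the plan says.** Under Outcome measurements, one secondary outcome is the "Cumulative rate of patients with upper gastrointestinal bleeding according to the modified TIMI criteria". The section then says that "the severity of upper gastrointestinal bleeding is classified into 3 grades" and writes out all three:

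- "major: clinically overt signs of hemorrhage associated with a drop in hemoglobin of ≥5 g/dL"
- "minor: clinically overt signs of upper gastrointestinal bleeding, resulting in hemoglobin drop of 3 to <5 g/dL"
- "minimal: any overt bleeding event that does not meet the criteria above"

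The same section lists "The cumulative rate of patients with all-cause death" among the other pre-specified outcomes, with no link to the bleeding grade.

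On hemoglobin, Scope of study data says that results "tested for the first time after admission are used as baseline data" and that "The above laboratory tests will be also collected and recorded at 6 and 12 months after randomization". Safety and adverse events separately has laboratory findings, treatment and outcome recorded for adverse events. It leaves out non-serious events that do not lead to stopping the study drug.

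**The concern.** Overt bleeding is common to all three grades, so only the hemoglobin drop decides between them. The residual clause sets no upper limit on clinical severity: whatever misses the two thresholds goes to the mildest grade. Two kinds of serious event can miss them for reasons unrelated to how serious they are.

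- **Fatal bleeds.** A patient may die when the last measured hemoglobin has fallen by less than 3 g/dL.
- **Transfused bleeds.** Red cells given before the lowest value is taken raise that value, so the measured drop understates the loss. The more blood a patient needed, the milder the grade can look.

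This is not detail left to a fuller document. The rule is printed in full, and followed as printed it gives the wrong grade. At stake is the table of bleeding severity by arm, in a trial whose Background presents GI bleeding as the harm of DAPT that PPIs are meant to reduce.

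**Working it through.** The plan gives no figure to reproduce here, so the check is to apply the printed rule to example bleeds.

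**Rule (Outcome measurements).** For an overt bleed with measured drop *d*: *d* ≥ 5 g/dL is major; 3 ≤ *d* < 5 is minor; otherwise minimal.

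**Fatal bleeds.** Death does not enter the rule, so the grade follows *d*:

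- *d* = 2.5: minimal
- *d* = 4: minor
- *d* = 5.5: major

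**Transfused bleeds.** Measured drop = true loss − units × rise per unit. The rise per unit is not in the protocol; I assume 0.8 to 1.2 g/dL.

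| True loss (g/dL) | Units | Measured drop at 0.8 / 1.2 per unit | Grade if untransfused | Grade as printed |
|---|---|---|---|---|
| 6 | 1 | 5.2 / 4.8 | major | major / minor |
| 6 | 2 | 4.4 / 3.6 | major | minor |
| 5 | 1 | 4.2 / 3.8 | major | minor |
| 5 | 3 | 2.6 / 1.4 | major | minimal |
| 4 | 1 | 3.2 / 2.8 | minor | minor / minimal |
| 4 | 2 | 2.4 / 1.6 | minor | minimal |

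For example, 6 − 2 × 0.8 = 4.4 and 6 − 2 × 1.2 = 3.6; 5 − 3 × 0.8 = 2.6 and 5 − 3 × 1.2 = 1.4. In four of the six rows the downgrade holds across the whole assumed range. In the two rows of 6 and 4 g/dL with a single unit, it depends on the rise assumed.

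**Reference value for the drop.** The grading text names none, and the article defines baseline in two ways. Scope of study data takes the first hemoglobin after admission. Statistical and analytical plans takes the last available assessment on or before the day of the first study dose. Participant recruitment screens patients after surgery, so the operation lies between admission and enrollment and the two values can differ. A transfusion correction needs one of them, or another stated value, to be fixed.

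**What the grade feeds.** The named outcome counts patients with upper GI bleeding. All three grades are overt bleeds, and no text restricts the count to major ones. A misgraded bleed is still counted once.

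**The case against.** The strongest reply is that little rests on the grade. The secondary outcome is bleeding of any grade. Neither Study objectives and hypothesis, Outcome measurements nor Statistical and analytical plans sets a major-bleeding rate as an endpoint or a test by grade. Deaths are counted separately, and Safety and adverse events gives a route for laboratory values, treatment and outcome at the time of the event. That section's exclusion of non-serious events would not remove a fatal bleed and is unlikely to remove one that needed several units. The grades are also attributed to a named scheme, and the printed text may shorten it. The last point cannot be checked here and does not change what the printed rule does. The rest stands and limits the impact; it does not repair the rule.

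Two stronger readings are tempting and are not supported.

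- **A reader might infer that any bleed without a hemoglobin value is automatically minimal.** Scheduled laboratory tests after randomization fall only at 6 and 12 months, and the 3- and 9-month contacts are by telephone. But the residual clause does not say that an unmeasured hemoglobin counts as failing the thresholds, unscheduled values have a recording route, and rules for missing values may stand in the full protocol or analysis plan. A separate category for ungraded bleeds is not needed on this evidence, and it would take mild bleeds reported by telephone out of the severity table.
- **A reader might infer that the rule conceals harm in one arm.** Every overt bleed still counts in the outcome, and every death is counted. With 232 / 2 = 116 per arm, one regraded event moves the proportion with major bleeding by 1 / 116 = 0.9 percentage points, but the protocol names no such rate as an endpoint and gives no expected number of bleeds.

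**Conclusion.** The concern holds for the severity breakdown only. As printed, the rule grades a fatal bleed with a measured drop below 3 g/dL as minimal and one of 3 to <5 g/dL as minor, and it can lower a transfused bleed by one or two grades. The fatal case follows from the text alone. The size of the transfusion effect rests on the assumed 0.8 to 1.2 g/dL per unit. How many events would be affected cannot be estimated, because the protocol gives no expected bleeding or transfusion rate; a fatal or transfused bleed with a large enough measured drop is still graded minor or major. The any-grade bleeding rate, the primary outcome and the sample size are untouched. The point is worth correcting because the error falls on the most serious bleeds and the correction is cheap.

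**What to change.** Amend the grading text under Outcome measurements, by the route described under Amendment and before bleeding events are tabulated by arm:

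1. Grade any fatal upper GI bleed as major, whatever the hemoglobin.
2. Define the drop as reference value minus nadir, plus units transfused between the two multiplied by a stated rise per unit. Name the reference value and resolve the two baseline definitions for this purpose.
3. State that grading uses the laboratory, treatment and outcome data recorded under Safety and adverse events.

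The cost is a few sentences and the regrading of a small number of events from records that the protocol already requires. No visits or patients are added. The downside is that a few events move to a more severe grade.

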### Definition of the end of study

The date on which the last subject completed the last follow-up was the endpoint of this studyDuring the follow-up period, if the patient’s biopsy pathological report showed that EGD detects precancerous lesions (e.g., atypical hyperplasia, low-grade or high-grade internal neoplasia, etc.) or malignant lesionsPatients randomized to the control group (1-month pantoprazole treatment group) should continue PPI treatment if GERD-Q questionnaire score ≥ 8, endoscopic findings of reflux esophagitis (LA-A and above), gastroduodenal mucosal injury of modified Lanza score of 4, or upper gastrointestinal bleeding at any time during the follow-up period

According to the ITT principle, all patients randomized in this study should be evaluated for primary and secondary endpoints regardless of changes in PPI treatment. Thus, patients in the 1-month pantoprazole treatment group required PPI treatment at any time after 1 month and could also be assessed for primary and secondary endpoints.

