### Follow-up

Patients will be followed up to 12 months post-randomization unless dead. The outcome will be collected at 2±1 day, 9±2 days, 1 month (30±7 days), 3 months (90±7 days), 6 months (180±14 days), 9 months (270±14 days), and 12 months (360±14 days) after CABG surgery, respectively. Among them, the visits at 3 and 9 months after randomization are telephone calls. Each subject’s survival status (surviving/deceased), blood pressure, heart rate, body mass index, waist circumference, and adverse events (AEs) will be recorded on the CRF after each conversation. At 6 and 12 months post-randomization, routine laboratory tests and anesthesia EGD will be performed respectively. The endoscopist in the present study who evaluated the upper GI mucosal injury was blinded to random treatment allocations. In addition, computed tomographic angiography (CTA) or coronary angiography (CAG) is also required at 12 months post-randomization. Face-to-face adherence reminder sessions will take place at the initial pantoprazole dispensing and each study visit thereafter.

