### Statistical and analytical plans

The primary analysis was conducted according to the intention-to-treat (ITT) principle. All randomized subjects were included in the ITT analysis set. Subjects who received at least one dose of study medication and continued to receive the randomized intervention regimen (with or without study medication) 1 month after CABG were defined as the modified full analysis set (mFAS) population. Among them, subjects who completed the treatment according to the randomized protocol without major protocol violations and had a primary outcome assessment were included in the per-protocol set. Effectiveness analysis will be performed on the basis of mFAS. The safety analysis set consists of all the subjects who had taken at least one dose of study medication.

In this study, all subjects received pantoprazole treatment for at least 1 month after CABG. Due to the COVID-19 pandemic, some subjects are unable to return to the center for study drugs and/or follow-up 1 month after the randomization. Those subjects who are unable to receive subsequent randomization intervention will be excluded from the mFAS and not included in the effectiveness analysis. Considering the statistical power of the study, randomized subjects will be added until the effective randomized intervention number reaches the predetermined sample size.

All statistical analyses will be performed using SAS version 9.4 (SAS Institute Inc. SAS/STAT, Cary, NC, USA). Unless specified otherwise, the number of subjects (*n*), mean, standard deviation, median, maximum, and minimum will be provided for continuous variables, and the number of subjects and the percentage will be provided for categorical variables.

The baseline in this study will be defined as the last available (non-missing) assessment (scheduled or unscheduled) before or on the same day as the first dose of study treatment.

The chi-square test will be applied as the main analysis of the primary efficacy endpoint, and multiple sensitivity analyses will be performed to support the main analysis. For secondary and exploratory efficacy endpoints, analysis of covariance, Wilcoxon-Mann-Whitney test, log-rank test, a mixed-effects model for repeated measures, and negative binomial regression model will be applied based on the type of data in the analysis. Descriptive statistics will be provided to summarize safety endpoints.

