### Safety and adverse events

Pantoprazole tablet has been used for more than 20 years, and the overall characteristics of its adverse reactions have been well described. This study mainly collects those AEs of particular concern related to PPI [20], such as chronic nephropathy, pathological fractures, myocardial infarction, pneumonia, spontaneous bacterial peritonitis, gastrointestinal tumors, and trace element deficiency. Non-serious AEs that did not cause discontinuation of the study drug will not be collected.

Participants showing any AE will be treated appropriately by doctors, and the project will cover the cost of AEs. Adverse reactions will be checked at every visit. For any AE that occurs, all details, including the time of occurrence, symptoms, signs, degree, duration, laboratory findings, treatment, outcomes, and causal relationship with the treatment, will be recorded in the CRF. Serious AEs will be reported to the Research Ethics Committee within 24 h, which will decide whether any additional measures should be taken. The total number of patients with AEs related to the study drug (certain, probable, possible) and the total number of patients with AEs leading to discontinuation of study treatment will be summarized.

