## Discussion

Our previous study (DACAB-GI-1), a single-center prospective substudy of a RCT (DACAB, NCT02201771) [20], provided important reference data for the subsequent design of the DACAB-GI-2 trial. Briefly, patients aged 18–80 years with indications for elective CABG surgery were randomized to 1 year of open-label antiplatelet therapy comprising ticagrelor 90 mg twice daily plus aspirin 100 mg enteric-coated tablet, once daily; ticagrelor alone (90 mg twice daily); or aspirin alone (100 mg once daily). Prophylactic use of PPI was not a randomized intervention. It was recorded at 1, 3, 6, and 12 months post-CABG. Data of both upper gastrointestinal mucosal injury assessed by EGD and *H. pylori* infection detected by ^13^C urea breath test were obtained only at 1 year post-CABG, not at baseline [12]. In the present study (DACAB-GI-2), 232 subjects on DAPT after CABG will be randomized into two treatment groups (12- vs. 1-month treatment of pantoprazole); ^13^C urea breath test is done before enrollment and EGD is performed at 6 and 12 months after randomization, respectively.

A PPI selected in the present study was pantoprazole. Compared with the other PPIs, pantoprazole has a lower affinity for CYP2C19 and has the least interaction with other kinds of drugs, so it has higher safety and is less likely to cause AEs in patients when used in combination with dual antiplatelet agents [6, 7]. Whether the P2Y_12_ receptor inhibitor is clopidogrel or ticagrelor, pantoprazole is suitable in combination with it. In the present study, all patients will be treated with pantoprazole for at least 1 month after CABG to reduce the risk of perioperative gastrointestinal bleeding.

Patients undergoing CABG are those with more advanced coronary artery disease. EGD will not be performed preoperatively, perioperatively, and within 6 months of surgery, except in cases of emergency [21], because it is not considered to be in the patients’ best interest. In the present study, EGD will be performed at 6 and 12 months after randomization. The purpose of designing the first EGD at 6 months is not only to establish self-control but also to help identify patients with asymptomatic ulcers on time. Of particular importance, the early stages of esophageal and gastric neoplasms are asymptomatic as well. These patients are considered to have reached the endpoint of the study if they are diagnosed by EGD and biopsy at 6 months post-randomization.

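### A neoplastic biopsy is listed as an end-of-study event, which conflicts with outcome follow-up to 12 months; the two must be reconciled so that the finding does not stop data collection

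*Protocol article*

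**What the plan says.** All references are to the protocol article.

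- **Definition of the end of study.** The list includes the case, at any time during follow-up, in which a "biopsy pathological report showed that EGD detects precancerous lesions" (examples are given) or malignant lesions. The item is a conditional clause with no stated consequence.
- **Discussion.** After mentioning asymptomatic ulcers and early neoplasms, the text gives a consequence: "These patients are considered to have reached the endpoint of the study if they are diagnosed by EGD and biopsy at 6 months post-randomization".
- **Follow-up.** "Patients will be followed up to 12 months post-randomization unless dead". EGD is scheduled at 6 and 12 months, graft imaging at 12 months, and telephone calls at 3 and 9 months.
- **Outcome measurements.** The other pre-specified outcomes run up to 12 months. They include "The cumulative rate of patients with MACE (composite of cardiovascular death, myocardial infarctions, or stroke"), graft failure on imaging, and "The cumulative rate of patients with all-cause death". Neoplasia is not listed as an efficacy outcome.
- **Intention to treat.** The paragraph that closes the end-of-study section says that "all patients randomized in this study should be evaluated for primary and secondary endpoints regardless of changes in PPI treatment". Statistical and analytical plans adds: "All randomized subjects were included in the ITT analysis set".
- **Safety and adverse events.** The events of particular concern include "chronic nephropathy, pathological fractures, myocardial infarction, pneumonia, spontaneous bacterial peritonitis, gastrointestinal tumors".
- **Data capture.** For subjects who withdraw early, the available efficacy and safety data must be entered. No section says that new data are collected after a neoplastic biopsy.

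**The concern.** Two stated rules cannot both be followed. A site working from the end-of-study list and the Discussion would close the patient's participation at the 6-month EGD. A site working from the Follow-up section would carry on to month 12.

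Under the first reading, a patient diagnosed at 6 months contributes no later survival, MACE or bleeding data, no separate later safety events, no graft imaging and no second EGD. Such an exit may be related to outcome, because a patient newly found to have a malignant or premalignant lesion need not have the same later risk as one who stays. If the log-rank test listed in the analysis section were used for such an outcome, censoring at diagnosis would assume no such relation. The trial also randomizes the duration of a proton pump inhibitor (PPI) and names gastrointestinal tumors among its events of particular concern. Observation would then stop on an event that the safety plan sets out to watch.

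The phrase about reaching the study endpoint adds a second uncertainty. It could be taken to count the lesion as an efficacy event, which the outcome list does not do.

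**Working it through.** **1. Does the list item end the patient's study?** Alone, it does not say so, because the clause is incomplete. Its heading and the Discussion sentence together give that meaning for a lesion found at the 6-month EGD. For a lesion found at the 12-month EGD, little follow-up remains to be lost.

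**2. Does the intention-to-treat paragraph restore follow-up?** Only in part. It covers changes in PPI treatment, which is the third list item (control patients who continue a PPI). A biopsy result is not a PPI change. It also covers primary and secondary endpoints, whereas MACE, graft failure and death are listed as other pre-specified outcomes. For these three the clear conflict is with Follow-up and Outcome measurements. Including all randomized subjects in the ITT set settles who is analyzed, not whether data are collected after month 6.

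**3. What is still captured?** The tumor diagnosis, and under the adverse-event rules its treatment and outcome, plus whatever data exist at exit. Later, separate events are not covered.

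**4. The plan's sample size, as the basis for sizing.** Inputs from Sample size: 36% vs 18%, two-sided α 0.05, power 80%, 1:1.

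- Pooled variance under the null, p̄ = (0.36 + 0.18)/2 = 0.27: n per arm = [1.960·√(2·0.27·0.73) + 0.842·√(0.36·0.64 + 0.18·0.82)]² / 0.18² = 94.3, so 95 per arm and 190 in total.
- Unpooled: (1.960 + 0.842)²·0.378 / 0.18² = 91.6, so 92 per arm and 184 in total.
- The stated 186 lies between the two. Dropout: 186/0.8 = 232.5 against the stated 232. The figure is reproduced to within rounding and choice of formula.
- Power at 93 per arm: Φ[(0.18·√93 − 1.960·√0.3942)/√0.378] = Φ(0.822) = 79.4%.

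**5. Size of the loss.** The documents give no lesion frequency f, so 0.5% to 5% is an assumption. Patients affected = 232·f. Share of planned patient-time lost = f·6/12, taking every lesion as found at 6 months. The power column takes 93·(1 − f) per arm, which supposes that none of these patients has a usable primary outcome.

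| f | Patients of 232 | Patient-time lost | Power |
|---|---|---|---|
| 0.5% | 1.2 | 0.25% | 79.2% |
| 1% | 2.3 | 0.5% | 79.0% |
| 2% | 4.6 | 1.0% | 78.6% |
| 5% | 11.6 | 2.5% | 77.3% |

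Both suppositions overstate the loss. Some lesions would be found only at 12 months, and the primary outcome counts lesions within 12 months, so the 6-month EGD still contributes.

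**The case against.** The strongest reply is that this is a wording problem. The list item is incomplete. The item after it concerns continued PPI treatment and is plainly not an end of study, since the text below it keeps those patients under assessment, so being on the list does not by itself prove that data collection stops. The Follow-up sentence is a general statement of schedule, and the Withdrawal section already foresees other early exits (patient choice, adverse events, protocol deviations, investigator discretion). Data capture and the adverse-event rules keep the tumor and its outcome on record. The number of patients is small, and the sample size already allows 20% dropout.

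Much of this stands. The loss of later events is an inference from how the rule would be applied, not something the text states. A reader might also infer more than the documents support:

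- that tumor events themselves go unrecorded, which the adverse-event rules contradict;
- that every affected patient leaves at month 6, although the list item covers the whole follow-up period;
- that event rates are necessarily underestimated, or that one arm is favored. No lesion rate, death rate or difference between arms is given, so neither the direction nor the size of a bias can be established.

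The reply does not remove the conflict. The Discussion attaches end-of-study wording to the 6-month diagnosis, the intention-to-treat sentence covers a different situation, and no section says that follow-up goes on. The withdrawal provisions show that other exits are foreseen. They do not reconcile a rule that makes a protocol-scheduled finding an end-of-study event with outcomes defined to month 12.

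**Conclusion.** The point holds as an unreconciled rule that, applied as written, gives avoidable and possibly outcome-related loss of follow-up in patients whose lesion is found at the 6-month EGD. It affects all-cause death, MACE, graft failure, bleeding and separate later safety events, together with the second EGD.

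It is modest in size: about 1 to 12 of 232 patients and at most 2.5% of planned patient-time, on the assumed lesion range. The primary comparison is barely touched, with a worst-case loss of about 2 percentage points of power. The documents do not support reading it as a threat to the primary result or as a demonstrated bias in either direction. It deserves correction because each affected patient would lose about half of the follow-up for the 12-month outcomes, and keeping that follow-up costs little.

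**What to change.** Reconcile Follow-up, Definition of the end of study and the Discussion so that a neoplastic biopsy does not end outcome data collection. Specifically:

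- State that survival, MACE, bleeding and serious adverse events are collected to 12 months at the existing visits and telephone calls.
- Use any 12-month EGD or graft imaging that is done in these patients, and keep their 6-month EGD in the primary endpoint.
- State that neoplasia is a safety outcome and not a primary event, and replace the wording about reaching the endpoint of the study.
- Leave decisions on study treatment and clinical management after such a finding to the investigators, separate from the rule on data collection.

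The cost is a short amendment with ethics approval and continued contact with a few patients. No procedure is added. Trial status reports 117 patients with completed 12-month follow-up and completion planned for June 2023, so at that date the change could still apply to patients in follow-up. For any patient already closed out on this ground, 12-month vital status and events could be sought, subject to consent.
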